## Abstract

**Introduction:**

Mixed-specifier mood disorders are probably a different subgroup in terms of response to treatment, socio-demographic parameters, course, and family history. Here we describe the rationale and design of a clinical trial aimed to test the efficacy, safety, and tolerability of a non-pharmacological treatment known as theta-burst stimulation (TBS) for treating the mixed depressive episodes of both bipolar (I or II), and unipolar depression.

**Methods:**

The study is designed as a randomized, sham-controlled, double-blinded clinical trial evaluating TBS for the treatment of moderate or severe major depressive episodes with mixed features of patients receiving at least one first or second-line pharmacological treatment for depressive episodes without adequate response. Ninety adult (18 to 65 years old) patients will be enrolled and submitted to 6-week (comprising 5 consecutive days a week sessions for the first 3 weeks and then 2 days a week for a further 3 week) of inhibitory followed by excitatory TBS in dorsolateral prefrontal cortex. Participants will be assessed using clinical and neuropsychological tests before and after the intervention. The primary outcome is change in Montgomery–Åsberg Depression Scale (MADRS) score over time and across groups. Cognitive parameters will also be assessed with neuropsychological tests.

**Results:**

The clinical results will provide evidence about TBS as an adjunctive treatment for mixed depression treatment and neuropsychological parameters will contribute toward an improved understanding the effects of TBS in cognition.

**Conclusion:**

Our results could introduce a novel therapeutic technique for mixed depressive episodes of both bipolar and unipolar disorders.

**Clinical Trial Registration:**

www.ClinicalTrials.gov, identifier NCT04123301; date of registration: 10/10/2019; URL: https://clinicaltrials.gov/ct2/show/NCT04123301?term=NCT04123301&rank=1.

## Introduction

Although overlapping depressive and (hypo) manic symptoms in mood disorder have been identified from the incipient descriptions of manic-depressive illness (1), current classifications have only appeared in the 4th edition of the Diagnostic and Statistical Manual of Mental Disorders (DSM-IV) in 1994 under the name of “mixed state” in which the complete manic syndrome and complete depressive syndrome would simultaneously occur in type I bipolar disorder (BD) patient (2). Important studies carried out last decade (3–9) in different forms of overlapping depressive, manic, and hypomanic symptoms have supported the concept of mood episode with mixed features of the 5th edition of the Diagnostic and Statistical Manual of Mental Disorders (DSM-5), that can be applied to any episode of BD I or II, but also of major depressive episode of major depressive disorder (MDD) (10). The mixed features specifier at DSM-5 is characterized by the presence of at least three symptoms of the opposite pole of the predominant mood episode (**Table 1**) (11), excluding the “DIP symptoms”: distractibility (D), irritability (I), and psychomotor agitation (P), with the preliminary justification that such symptoms have been described in both (hypo)manic and the depressive episodes in the current classifications. Studies prior to (7–9) and later (12–15) to the publication of the DSM-5 demonstrate that the exclusion of “DIP symptoms” is not corroborated by scientific evidence. The presence of mixed features in any mood episode, especially the depressive episodes, has been associated with higher comorbidities, higher relapse rates, worse clinical outcomes, and higher suicide risk in BD patients and has been evaluated in several studies (16–20), although it has not yet been adequately studied in depressive episodes with mixed features of MDD. A recent review (21) showed that the percentage of mixed features ranged from 4.3% (22) to 58.6% (23) in BD and from 0% (22) to 34% (23) in MDD, much depending on each study criteria. These extremely wide variations may be due to the low sensitivity of the mixed feature specifier adopted by the DSM-5 (5.1%) (24).

**Table 1 T1:** Depression with mixed features specifier (DSM-5).

**Mixed depression (3 or more of the following during a major depressive episode):** (1) expansive or elevated mood; (2) increased self-esteem or grandiosity; (3) more talkative than usual or speaking pressure; (4) flight of ideas or subjective sensation that thoughts are running; (5) increased energy or goal-directed activity (socially, at work or at school); (6) increased or excessive involvement in activities with high potential for bad consequences (eg, rampant shopping, sexual indiscretion, unwise business investments); (7) reduced need for sleep (feeling rested despite sleeping less than usual).

DSM-5, 5th edition of the Diagnostic and Statistical Manual of Mental Disorders.

Transdiagnostic approaches aim to identify factors that occur regardless of the diagnostic construct that may play a role in initiating and/or maintaining different disorders. According to transdiagnostic approaches risk factors for a specific disorder may also confer risk for other disorders, especially those that share symptoms. Rather than examining risk factors for each specific disorder, this paradigm suggests that a better approach to understand the pathophysiology would be to focus on transdiagnostic factors that may contribute to the development of many forms of psychopathology (25, 26). Mixed features in the context of different mood disorders go in the same direction as this approach. Another aspect that has been recently studied and which meets these transdiagnostic approaches is the alteration of biological rhythms in mood disorders (27). Changes in chronobiological rhythms have been described in both MDD and BD (28). The investigation of changes in biological rhythms in depression with mixed features of MDD or BD has not been adequately investigated (29, 30).

Repetitive transcranial magnetic stimulation (rTMS) is widely known treatment option for MDD (31). A recent rTMS meta-analysis in the treatment of depressive episodes indicates that the technique yields statistically significant results improving 30% of patients receiving active excitatory rTMS compared to 10% of patients receiving sham treatment (analysis based in 29 randomized, double-blind, and controlled clinical trials) (32). Recently, a new form of rTMS, the theta-burst mode stimulation (TBS) was introduced and appears to produce at least similar effects on brain activity than standard rTMS (33–36). In addition to greater efficacy, the reduced duration of administration may be another advantage of TBS compared to conventional rTMS procedure, standard TMS sessions last about 45 min, whereas TBS requires less than 10 min of stimulation (33, 37). There are two types of TBS stimulation: intermittent (iTBS) and continuous (cTBS), with facilitating and inhibitory effects, respectively (36). Recent evidence is growing about TBS use in treatment resistant depression (38). Despite the growing number of studies on BD neuroimaging in recent years, the brain regions involved in mood dysregulation in episodes with mixed features have been poorly studied. If some neurofunctional abnormalities appear to be independent of mood state, others appear to be preferentially associated with mania or depression involving the amygdala and other limbic regions, as well as frontal ventral regions, with possible hemispheric lateralization of these anomalies according to mood state patient (36). The few mixed state neuroimaging studies so far support the hypothesis of lateralization of brain abnormalities in relation to bipolar symptomatology, suggesting that neurofunctional abnormalities preferably located in the frontal and limbic areas of the right hemisphere may be associated with the depressive component whereas abnormalities similar left regions would be associated with the manic component (39). Few studies have evaluated the efficacy of TMS in mixed depressive states alone. A recent open study has shown that low frequency (inhibitory) of repetitive (non-TBS) TMS on the right dorsolateral prefrontal cortex (DLPFC) for 3 weeks led to a response and remission rate of 46% and 28%, respectively, in depressive episodes with mixed features of type I BD (40). On the other hand, a study with TBS modality showed that bilateral stimulation (right cTBS and left iTBS) produced greater results in treating major depressive episodes of MDD than unilateral stimulation (41).

As the DSM-5 definition of mixed features has been recently published, treatment guidelines that provide recommendations for treating mixed episodes are still limited (42). Some authors suggest that data from clinical trials using mixed episodes defined by DSM-IV-TR may guide the treatment of mood episodes with mixed features defined by DSM-5, but with certain caveats (42). The DSM-IV definition of mixed episodes was restrictive and as such cannot be applied to the current definition of mixed states in DSM-5, with the caveat that the current definition does not yet understand DIP symptoms and that recent studies shows that DIP symptoms are likely to be cardinal symptoms of mixed states (17). In addition, these previous studies were conducted in patients with bipolar I disorder, whose results cannot be applied to mixed states of BD II and MDD (43). Mixed specifier of mood disorders (TB and MDD) are probably a different subgroup in terms of clinical response to treatment, socio-demographic parameters, course (frequency of recurrences, predominant polarity, etc.), and family history (44).

The main objective of this study is to evaluate the efficacy and safety of TBS as an add-on treatment for mood stabilizers (in BD I and II) or antidepressants (in MDD) in moderate and severe major depressive episodes with mixed features. Therefore, TBS will be combined to pharmacological treatments of patients who are adequately treated with first or second-line drugs to treat a mixed depressive episode of either MDD (antidepressants) or BD (mood stabilizers), according to CANMAT, and still present with moderate or severe mixed depression. In addition, the study aims to evaluate the impact of restrictive (without “DIP symptoms”) and broad (considering “DIP symptoms”) criteria on treatment-related factors and other clinical features.

## Methods

### Design and Study Population

This will be a randomized, double-blind, sham-controlled, 6-week clinical trial, comprising 5 consecutive days a week sessions for the first 3 weeks and then 2 days a week (interval at least 1 day between sessions) for a further 3 weeks of active or sham TBS. The study will be conducted at the Institute of Psychiatry of the School of Medicine of the University of Sao Paulo (HCFMUSP). The study will be conducted in accordance with the principles established by the Declaration of Helsinki (45) and the American Document of Good Clinical Practice (46). This protocol have been published in www.clinicaltrials.gov with the number NCT04123301.

Ninety adult patients aged 18 to 65 years with a diagnosis of type I BD, type II BD or MDD in moderate or severe depressive episode (according to DSM-5 criteria) with mixed features (according to DSM-5 criteria plus symptoms of distractibility, irritability and psychomotor agitation). The diagnosis will be confirmed by the Portuguese version of the structured interview of DSM-IV (Structured Clinical Interview—SCID IV) (47) modified with the DSM-5 criteria and specifiers without the exclusion of symptoms distractibility, irritability, and psychomotor agitation, since there isn't a Portuguese version of the SCID of DSM-5. Recruitment strategies will include referrals from other doctors and advertising at internet and newspapers. Participants will be randomized using a computer generated list for one of two intervention groups (in a 1:1 ratio) to the active or sham TBS group. Allocation masking will be done by sequentially numbered cards that will determine which group each patient belongs to. The card determines whether the coil to be used will produce active or sham stimulation. A person not directly involved in the clinical trial will be responsible for delivering the sham or true coil according to randomization, remembering that the coils are physically identical and have similar sound properties and stimuli. Participants and staff will be unaware of the status of allocation groups.

### Inclusion and Exclusion Criteria

Eligibility criteria is the presence of manic polarity symptoms during a moderate or severe depressive episode of BD I, BD II or MDD. We set the Montgomery–Åsberg Depression Rating Scale (MADRS) (48) with a score between 20 and 34 points for the definition of moderate major depressive episode and above 34 points for severe major depressive episode. The definition of major depressive episode with mixed features will be performed using the Young Mania Rating Scale (YMRS) (49) with ≥1 point on three or more items according to criteria used in the International Mood Disorders Collaborative Project (12) and consist with other definitions of depression with mixed features (50–53). Patients will be included in any appropriate pharmacological regimen (first or second line) according to the Canadian Network for Mood and Anxiety Treatments (CANMAT) guidelines to treat a major depressive episode of MDD or BD (I or II) (54, 55) and still have mixed depressive symptoms, so that TBS will be applied as an add-on treatment. We will not make adjustments to patient treatments, we will only enroll patients that are already on a stable psychopharmacological regimen (at least one month) of first or second line according to CANMAT but with no response/remission or partial response (still meeting inclusion criteria). The pharmacological regimen should be maintained on the same schedule and dosage from the beginning to the end of the study and patients will not be in a psychotherapy regimen. Drugs such as benzodiazepines will only be allowed at low doses (less than 3 mg per day of lorazepam or equivalent). Exclusion criteria will be: concomitant diagnosis of other neuropsychiatric disorders such as: schizophrenia, dementias, mental retardation, organic mental disorder, or epilepsy; psychotic depression; acute suicide ideation (assessed by interview and clinical evaluation); suspected or confirmed pregnancy; women in breastfeeding; severe or unstable clinical disease; specific contraindications to TBS (previous epileptic seizures; change in electroencephalogram at some point in life; previous stroke; previous severe TBI (with neurosurgery); metallic object on head (except mouth) as projectile piece, surgical clip, welding fragments; any implanted device (cardiac pacemaker, intravenous catheter). Personality, anxiety, and substance use disorders will be allowed as comorbidity provided the primary diagnosis is BD or MDD.

Clinical assessments will be conducted weekly until the end of week 3 and thereafter a final assessment will be conducted at the end of week 6. Adverse events will be evaluated every day during the first week and then once a week until the end of the week 6. The neuropsychological assessment battery will be applied before the patient is stimulated and at the end of the week 6 of intervention (**Table 2**).

**Table 2 T2:** Measurement outcomes over time.

Scales	Baseline	End of week 1	End of week 2	End of week 3	End of week 6
SCID I/P modified	X				
MADRS	X	X	X	X	X
YMRS	X	X	X	X	X
*WHOQOL-bref*	X	X	X	X	X
BIS-11	X	X	X	X	X
CGI-S	X	X	X	X	X
GAF	X	X	X	X	X
HAM-A	X	X	X	X	X
BRIAN	X	X	X	X	X
Morningness–Eveningness Questionnaire	X				
TMS' Typical side Effects Scale	X	X	X	X	X
UKU-SERS	X	X	X	X	X
Neuropsychological Assessment	X				X

SCID, Structured Clinical Interview; MADRS, Montgomery–Åsberg Depression Scale; YMRS, Young Mania Rating Scale; WHOQOL, World Health Organization questionnaire; BIS-11, Barratt Impulsivity Scale; GAF, Global Assessment of Functioning; HAM-A, Hamilton Anxiety Scale; BRIAN, Biological Rhythm Interview of Assessment in Neuropsychiatry; TMS, transcranial magnetic stimulation; UKU-SERS, Udvalg for Kliniske Undersøgelser Side Effect Rating Scale; CGI-S, Clinical global impression - Severity.

### Study Hypothesis

The main hypothesis of this study is that the active TBS on the right and left DLPFC in patients with mixed depression can produce a greater and statistically significant reduction in the primary outcome scale (MADRS) compared to sham TBS. Other aims of the study will be evaluate: TBS safety and tolerability; socio-demographic and clinical profiles; impact of DSM-5 mixed features with and without DIP symptoms; impact of DSM-5 anxiety features; impact of biological rhythms in mixed depression; impact of impulsivity on mixed depression; and impact of mixed depression in functionality.

### Measurement of Variables and Outcomes

This study will analyze:

Socio-demographic variables: age, gender, marital status, number of children, years of education, income status;Clinical features along the life: medical and psychiatric comorbidities, daily consumption of coffee or black tea or energy drink or cola or tobacco, family history of mood disorder, psychotherapy at the moment, electroconvulsive therapy in the past, number of mood episodes, number of previous hospitalizations, predominant polarity (manic, hypomanic or depressive), previous depressions specifier (melancholic or atypical), past of psychotic depression;Depressive symptoms at the present episode: depressed mood, anhedonia, increase or reduction in appetite, insomnia or hypersomnia, psychomotor retardation or agitation, fatigue/loss of energy, impulse reduction such as indecision, procrastination, abulia, excessive or inappropriate guilt, low concentration, thoughts of death, suicidal thoughts or suicide attempts);DSM-5 mixed features (hypomanic symptoms during depression): reduced need for sleep, acceleration of thoughts or flight of ideas, grandiosity or high self-esteem, increased energy or directed activity, pressure to speak or flight of ideas, increased impulsivity (sex, expenses/gifts/donations; games/bets; mobile use/internet use, drugs, stimulant substances as coffee, energy drink or amphetamines, smoke, abuse of painkillers, anxiolytics, muscle relaxing drugs and hypnotics, food compulsion, love obsession, excessive jealousy, impulsive change of look, tattoos and piercings, work or study compulsion) without and with DIP symptoms (distractibility, irritability and psychomotor agitation);DSM-5 anxious features: apprehensive expectation, tension or worry, feeling restless, difficulty concentrating on worrying thoughts, fear that something terrible might happen, feeling that you can lose control of yourself;Other suggestive symptoms of mixed depression: intensification of depressed mood characterized by anguish, distress, despair or restlessness, high mood lability, hyper reactivity to environmental stressors, sleep-wake cycle dysregulation characterized by difficulty turning off at night and getting out of bed in the morning, auto-aggressiveness or self-mutilation.

Primary outcome will be change in MADRS from baseline to week 3. Secondary outcomes will be: change in YMRS at the end of week 3 and 6 of treatment; response rates (50% or more of reduction in MADRS at the end of weeks 3 and 6 of treatment); remission rates (MADRS <11 (56) at the end of weeks 3 and 6 of treatment); change in anxious symptoms assessed by Hamilton Anxiety Scale (HAM-A) (57) at the end of weeks 3 and 6 of treatment; change in overall clinical impression assessed by Global Clinical Impression of Severity (GCI-S) (58) and Global Assessment of Functioning (GAF) (59) at the end of weeks 3 and 6 of treatment; change of functionality assessed by abbreviated version of the World Health Organization questionnaire (WHOQOL) (60) at the end of weeks 3 and 6 of treatment; change of biological rhythms assessed by the Biological Rhythm Interview of Assessment in Neuropsychiatry (BRIAN) (61) at the end of weeks 3 and 6 of treatment; change of impulsivity assessed by Barratt Impulsivity Scale (BIS-11) (62) at the end of weeks 3 and 6 of treatment; association between the chronotype assessed by Morningness–Eveningness Questionnaire (63) and the severity of mixed depression assessed by MADRS; and change in neuropsychological battery parameters before and at the end of the intervention (6 weeks).

Serious adverse events associated with the technique such as seizures is very rare if standardized pacing parameters are used (64). The most commonly observed side effects are facial muscle contractions, mild headache and facial pain. Other side effects include tinnitus, dizziness and nausea (65). To assess side effects, we will use a standardized scale by our service that tracks common side effects in transcranial magnetic stimulation (headache, cervical pain, physical tension, scalp pain, scalp burning, dizziness, nausea, hearing impairment, difficulty of concentration, mental confusion, positive mood, negative mood, convulsion). Data will be quantified for the presence of symptoms (1—absent, 2—mild, 3—moderate, and 4—strong) and for the relationship that the patient attributes to the stimulation (1—none, 2—remote, 3 – possible, 4—probable, and 5—definitive). Concomitantly we will assess side effects by the Udvalg for Kliniske Undersøgelser Side Effect Rating Scale (UKU-SERS) (66). This scale assesses side effects related to psychiatric symptoms, neurological symptoms, autonomic symptoms, and other symptoms. The severity of each item varies in levels from 0 to 3. Blinding efficacy will be assessed at the end of week 6 by asking TBS appliers and participants about their allocation group.

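### The in-house TMS side-effect scale, as listed, has no item for facial muscle contractions, facial pain or tinnitus, although the protocol ranks the first two among the three most common effects

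*Protocol article*

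**What the plan says.** Safety and tolerability are a declared aim. The protocol article (Study Hypothesis) says: "Other aims of the study will be evaluate: TBS safety and tolerability". The main objective at the end of the Introduction also pairs efficacy with safety.

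Measurement of Variables and Outcomes gives the expected side effects first: "The most commonly observed side effects are facial muscle contractions, mild headache and facial pain". The next sentence adds tinnitus, dizziness and nausea.

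The section then introduces the instrument: "we will use a standardized scale by our service that tracks common side effects in transcranial magnetic stimulation". Its items follow in brackets: "headache, cervical pain, physical tension, scalp pain, scalp burning, dizziness, nausea, hearing impairment, difficulty of concentration, mental confusion, positive mood, negative mood, convulsion". Each is coded 1 to 4 for severity and 1 to 5 for how far the patient attributes it to the stimulation.

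Two further routes exist. UKU-SERS is given alongside, with each item graded 0 to 3, and is described by domain only: "This scale assesses side effects related to psychiatric symptoms, neurological symptoms, autonomic symptoms, and other symptoms". Table 2 schedules both scales at baseline and at the end of weeks 1, 2, 3 and 6. The text just above that table, under Inclusion and Exclusion Criteria, adds: "Adverse events will be evaluated every day during the first week and then once a week until the end of the week 6".

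**The concern.** Within one paragraph, the list of effects the authors expect and the list of effects their own TMS scale asks about do not agree. The scale is presented as following common effects, yet two of the three effects called most common are not on it. The items are printed as a complete list, with no wording that marks them as examples, so this is a mismatch in what the article states. It is not a detail left to a fuller document.

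An effect with an item is asked about at every rating, graded, and attributed by the patient in the same way in both arms. An effect without an item depends on some other route. If the tolerability table is built from the listed items, it will have no row for facial contractions or facial pain, and a reader could take the missing row to mean that the effect did not occur.

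**Working it through.** No sample size, power or error-rate figure bears on this point, and the plan states no figure to reproduce. The check is an item-by-item match inside Measurement of Variables and Outcomes, followed by a look at the other recording routes.

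**Step 1: named effects against the 13 items of the in-house scale.**

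| Effect named | How the article ranks it | Matching item | Nearest other item |
|---|---|---|---|
| Facial muscle contractions | most common | none | physical tension |
| Mild headache | most common | headache | – |
| Facial pain | most common | none | scalp pain |
| Tinnitus | other | none | hearing impairment |
| Dizziness | other | dizziness | – |
| Nausea | other | nausea | – |

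The nearest items are not equivalents. The scalp is a different site from the face, general tension is not a muscle contraction in the face, and loss of hearing is not tinnitus.

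**Step 2: counts.**

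- All named effects without an item: 3 of 6, 3/6 = 50%.
- Effects called most common without an item: 2 of 3, 2/3 = 67%.

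These are shares of named effects, not shares of toxicity missed.

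**Step 3: could another route record the three effects?**

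| Route | Schedule | Severity grade | Patient attribution | Shown to cover the three effects? |
|---|---|---|---|---|
| In-house TMS scale | baseline, weeks 1, 2, 3, 6 | 1–4 | 1–5 | No; the list lacks them |
| UKU-SERS | baseline, weeks 1, 2, 3, 6 | 0–3 per item | not described | Not shown either way; four domains, no item list |
| Adverse event evaluation | daily in week 1, then weekly to week 6 | not described | not described | Not shown either way; no method or items given |

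**Step 4: size of any under-recording.** This would need the incidence of the three effects in each arm and the fraction that the other two routes record. The article gives neither, so no number can be computed.

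**The case against.** The strongest reply is that the in-house scale is not the only safety net. UKU-SERS is given at the same visits, grades every item, and has neurological and other-symptom domains where these effects could fall. Adverse events are evaluated daily in week 1 and weekly afterwards. That is a different timetable from the scales, and nothing limits it to the 13 items. No sentence says that the tolerability comparison will use the in-house scale alone; Statistical Analysis says only which analysis set the safety comparison uses. The form itself is not shown and may have a free-text line.

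This stands, and it rules out several stronger readings that a reader might infer:

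- **That the trial will undercount these effects, or that they are absent from every rating.** The article shows only that they lack an item on one of two scales. Without the UKU-SERS items or an incidence, a definite undercount is not established.
- **That the gap biases the comparison toward good tolerability because facial effects differ most between active and sham.** Nothing in the article supports a difference in facial sensation between arms. Design and Study Population describes the two coils as identical in appearance and alike in sound and stimuli. The direction of any bias is therefore unknown.
- **That the gap removes the means of judging unblinding.** Participants and those applying the stimulation are asked at week 6 which group they think was allocated, and several scalp and tension sensations are recorded. At most, some information that might help explain those guesses is missing.

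The reply does not close the mismatch itself. Possible capture elsewhere is not the same as an item asked of every patient, and neither other route is described as recording attribution to stimulation.

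**Conclusion.** The point holds in a limited form. As listed, the TMS-specific scale does not ask about facial muscle contractions, facial pain or tinnitus: 3 of the 6 effects that the article names and 2 of the 3 it calls most common. The solicited comparison of active with sham may under-record these expected local effects, and the article describes no patient attribution for them. The amount cannot be computed.

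This rests on two assumptions: that the printed list is the whole scale, and that the other two routes do not already ask about these effects in a comparable way. If the form or the UKU-SERS item list shows otherwise, the gap narrows to the missing attribution rating, or closes.

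The point concerns a stated aim other than the primary outcome. The MADRS analysis, the sample size and the blinding procedure are not affected. It is a cheap improvement to make rather than a flaw that threatens the trial.

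**What to change.** Add three items to the in-house scale: facial muscle contractions, facial pain and tinnitus. Use the existing 1–4 severity and 1–5 attribution codes, at the visits where the scale is already given. Give each its own row in the between-arm tolerability table. For ratings made before the change, code the items as not collected, never as absent, and report the number of patients actually rated on each.

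The cost is three more lines on an in-house form and in the database, a slightly longer rating, and incomplete data on these items for patients already rated. The Conclusion says recruitment was not complete at submission; if that is still so when the change is made, later patients can be rated in full.
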